#### Secondary outcomes

All repeated measures of secondary outcomes will be modelled using the same approach as for urinary THC-COOH. That is, random slopes mixed-effects models for repeated measures regressions with group, time, the group × time interaction, number of counselling sessions attended, and whether or not NRT was taken as the fixed factors. These models will all be based on the generalised linear model, with link functions differing depending on the form of the outcome, as follows:Numeric (e.g., PROMIS-29 scores, marijuana craving questionnaire scores): Gaussian regression with identity link functionOrdinal (e.g., motivation to change cannabis use): ordinal logistic regression with logit link functionBounded count (e.g., severity of CUD) or binary (e.g., participant rating of group allocation): binomial logistic regression with logit link functionUnbounded count (e.g., adverse event count): negative binomial regression with log link function

See Table 1 for the form of each outcome measure.

Several secondary outcomes are single observations per individual. Group, number of counselling sessions attended, and whether or not NRT was taken will be the sole predictors in these models. Total abstinence from cannabis during weeks 10–13 (non-abstinent vs abstinent) and 50% increase in cannabis-free days during weeks 10–13 relative to cannabis-free days prior to baseline (< 50% reduction vs ≥ 50% reduction) will be modelled with binary logistic regression with logit link function, relative risk of adverse events during the trial period with negative binomial regression with log link function, hazard of treatment dropout via discrete-time hazard model with complementary log–log link function.

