### Participants and recruitment

#### Eligibility criteria

The target study population is treatment-seeking adults with moderate to severe CUD under conditions of informed consent. Eligibility will be assessed by an Addiction Medicine or Psychiatry credentialed Study Medical Officer (SMO).

Inclusion criteria*:*Aged 18 to 65 years.Meeting DSM-5 criteria for moderate or severe CUD (≥ 4/11 criteria) [2], with recent frequent cannabis use (≥ 4 days per week in the preceding 4 weeks).Willing and able to provide informed consent to study procedures.Proficient in English at a conversational level sufficient to participate in a counselling intervention.

*Exclusion criteria* aim to exclude individuals with conditions that jeopardise safety or confound data interpretation:Prescribed medicinal cannabis products (e.g., CBD, THC) for any indication in the previous 4 weeks.Another active (past year) moderate-severe substance use disorder other than tobacco; determined on clinical assessment using DSM-5 criteria.Active or severe medical (e.g., pain, epilepsy, cardiovascular disease) or psychiatric (e.g., psychosis, severe affective disorder) conditions based on clinical assessment.Moderate to severe hepatic disease (transaminase elevations > 3 times, bilirubin > 2 times upper normal limits at screening).Pregnant or lactating women (based on urine β-hCG at screening).Hypersensitivity to CBD or any excipients of Investigational Product.Using medications with known drug-drug hepatic CYP-450 interactions with CBD: 3A4, (e.g., carbamazepine, fluvoxamine, methadone), 2C19 (e.g., rifampin); CYP2B6 (e.g., bupropion), CYP2C9 (e.g., warfarin).Not available during treatment or follow-up (e.g., travel, impending residential detoxification or residential rehabilitation admission, impending imprisonment).Court-mandated treatment requiring abstinence from drugs.Current active (counselling and/or medication-based) treatment for CUD.Received an investigational medicinal product within the last 4 weeks (or 5 half-lives if using long-acting investigational drugs).

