#### Participant numbers

Sample size calculations are based on the analysis of the primary outcome, that is, the difference between placebo and CBD groups in total number of Cannabis-free Days over the 12-week intervention period. Ferguson has suggested that the minimum effect size (Cohen’s *d*) for an effect of practical clinical significance is 0.4167 [55]. To achieve 90% power (two-tailed) and α = 0.05, a total of *N* = 250 (*n* = 125 per group) participants are needed to detect a between-group effect size of *d* = 0.41. Of the target 250 sample, it is estimated approximately 20% (*n* = 50) of the study sample (*N* = 250) will be Indigenous Australians.

Participants who discontinue study procedures after commencing study interventions (medication dispensed on Day 1) will not be replaced in the study but will be included in the modified intention-to-treat analyses. Participants enrolled and randomised, but do not commence any treatment (no medication dispensed or other clinical interventions) will not be included in the final analysis.

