**Cannabis Use**	Modified Time Line Follow Back (TLFB) [64]	Cannabis free days, self-reported using a modified timeline follow back (TLFB). Week 1 and 25 interviews will ask about cannabis use in the preceding 4-weeks; week 4, 7, 10 and 13 interviews will ask about the preceding 3-weeks. Bounded count; number of days abstinence (out of 84)	Research Interview: Week 1 (baseline), 4, 7, 10, 13 and 25
	Diagnostic & Statistical Manual of Mental Disorders (DSM-V) [65]	Severity of Cannabis Use Disorder in the prior 12-weeks using the modified (DSM-5 criteria) MINI scale. Number of DSM-5 CUD criteria met out of 11 (Mild CUD: 2–3; Moderate CUD: 4–5; Severe CUD: 6 +) Bounded count, number of DSM-5 CUD criteria met (out of 11)	Research Interview/ Clinical review: Week 1 (baseline), 13 and 25
	Cannabis Use History	7 semi-structured questions exploring: history and frequency of cannabis use and any previous attempts at reducing cannabis use. Continuous	Research Interview/ Clinical review: Week 1 (baseline)
	The Substance Use Goals Questionnaire (SUG)	Bespoke scale developed by addiction medicine specialists involved in the CBD-CUD Study. Participants goal towards their cannabis use. Measured using a self-reported substance use goals questionnaire: 2 items with 5 response categories. 5-level ordinal	Research Interview: Week 1 (baseline), 4, 7, 10, 13 and 25
	Rates of Abstinence	The proportion of participants who achieve pre-identified levels of abstinence from cannabis use (weekly rates), and a 50% reduction in cannabis use days compared to the pre-treatment 4-week period. Binary categorical (non-abstinent vs abstinent)	Research Interview: Week 1 (baseline), 4, 7, 10, 13 and 25
	Cannabis Withdrawal Scale (CWS) [51]	19 items on a 10-point Likert Scale, with 0 = Not at all to 10 = Extremely. The CWS is used as a diagnostic instrument to assess severity of cannabis withdrawal symptoms. Self-report over the last 24 h in 8 domains; irritability, depression, anxiety, cannabis cravings, physical symptoms, sleep difficulty, restlessness and appetite. Continuous (average item score as a 0–10 range, converted to a z-score)	Research Interview: Week 1 (baseline), 4, 7, 10, 13 and 25

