#### Primary outcomes

We will model the effects of CBD on number of cannabis free days (out of 84 days) via single-level Gaussian regression with the outcome regressed on the main covariate experimental group (placebo vs CBD). Number of cannabis-free days in the 28 days prior to baseline will be included as a covariate to control for variation in participants’ prior frequency of use entering the study. Two treatment factors that could plausibly influence the primary outcomes and which vary across participants will also be included as covariates: number of counselling sessions attended during the study period (count variable range 0–4), and whether or not NRT was taken (binary variable measured at baseline: did not undertake NRT vs undertook NRT). If residuals are distributed normally, we will report the results from this analysis. If residuals are not distributed normally, we will treat cannabis-free days/84 as a bounded count instead of a numeric variable and use aggregated binomial regression with a logit link.

We will model urinary THC-COOH levels (a continuous outcome, in ng/MoL) via random-slopes mixed-effects models with the group, time (6-level categorical ordered predictor; Weeks 1 (baseline), 4, 7, 10, 13), the group × time interaction, number of counselling sessions attended, and whether or not NRT was undertaken as the fixed factors, and participant ID as the random factor.

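### The secondary 50% response outcome is defined by use days in Table 1 and by cannabis-free days in the analysis section, and the two rules select different responders

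*Protocol article*

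**What the plan says.** Table 1 of the protocol article, in the row on rates of abstinence, defines the response outcome as "a 50% reduction in cannabis use days compared to the pre-treatment 4-week period". The data analysis section on secondary outcomes, which specifies the logistic model, names the variable as a "50% increase in cannabis-free days during weeks 10–13 relative to cannabis-free days prior to baseline" and gives its categories as "< 50% reduction vs ≥ 50% reduction".

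The recall windows are in the Time Line Follow Back row of Table 1. For the on-treatment visits, "week 4, 7, 10 and 13 interviews will ask about the preceding 3-weeks". For the other two, "Week 1 and 25 interviews will ask about cannabis use in the preceding 4-weeks". The primary outcomes section confirms the 28-day baseline through its covariate: "Number of cannabis-free days in the 28 days prior to baseline". Eligibility requires "recent frequent cannabis use (≥ 4 days per week in the preceding 4 weeks" and closes the bracket there.

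Neither place says whether counts are converted to proportions of days, or what happens when baseline free days are zero.

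**The concern.** An increase in free days and a reduction in use days are different variables. They would be interchangeable only if both were expressed on the same base, and a percentage change is not. In a population that uses on most days, free days are few, so 50% of them is a small amount. Use days are many, so 50% of them is a large amount. A binary variable coded from the analysis section would therefore not be the one Table 1 describes.

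The article's introduction says that abstinence may not be the main goal for people who use cannabis. A reduction-based responder rate is thus one of the results readers will look at. With two published definitions, the choice could be left until after database lock and unblinding, when results are visible.

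A second, separate question is whether a 21-day count is to be compared with a 28-day count.

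**Working it through.** **The plan's own figure.** The article gives no number for this outcome. Its only calculated figure is the sample size for the primary outcome (d = 0.41, two-sided 0.05, 90% power): 2 × (1.960 + 1.282)² / 0.41² ≈ 125.0 per group, or 126 after rounding up, against a stated 125. That reproduces and does not depend on the point here.

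**Inputs.**
- Baseline window: 28 days (Table 1; primary outcomes section).
- End-of-treatment window: 21 days, reading weeks 10–13 as the interval between the week 10 and week 13 interviews (Table 1, three-week recall).
- Baseline free days F: use on at least 4 × 4 = 16 of 28 days gives F = 0 to 28 − 16 = 12. This is approximate, because eligibility is assessed at a screening visit up to four weeks before enrolment.

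**Rules**, with f free days out of 21 on treatment:
- Free-day rule, raw counts: f ≥ 1.5F.
- Free-day rule, proportions: f/21 ≥ 1.5F/28.
- Use-day rule, raw counts: 21 − f ≤ 0.5(28 − F).
- Use-day rule, proportions: (21 − f)/21 ≤ 0.5(28 − F)/28.

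For each rule, take the smallest whole f that qualifies. The fall in the rate of use is then 1 − [(21 − f)/21] / [(28 − F)/28].

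Example, F = 1, free-day rule: f ≥ 1.5, so f = 2. The rate goes from 27/28 = 96.4% to 19/21 = 90.5%, a 6.2% fall.

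Smallest fall in the rate of use that makes a responder:

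| F of 28 | Free-day, raw (f needed) | Free-day, proportions | Use-day, raw | Use-day, proportions |
|---|---|---|---|---|
| 0 | undefined, or 0% (0) | undefined, or 0% | 33.3% | 52.4% |
| 1 | 6.2% (2) | 6.2% | 35.8% | 50.6% |
| 2 | 7.7% (3) | 7.7% | 33.3% | 53.8% |
| 4 | 16.7% (6) | 11.1% | 33.3% | 50.0% |
| 8 | 40.0% (12) | 20.0% | 33.3% | 53.3% |
| 9 | 50.9% (14) | 29.8% | 36.8% | 50.9% |
| 12 | 75.0% (18) | 41.7% | 33.3% | 50.0% |

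**How often the rules disagree.** There are 13 × 22 = 286 combinations of F and f. On proportions, 77 are responders under the free-day rule only and none under the use-day rule only. On raw counts, 28 are free-day only and 15 use-day only, 43 in all. These are counts of possible combinations, not of expected participants.

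**What the windows do by themselves.**
- Use-day rule, raw: 28 of 28 days falling to 14 of 21 scores as a halving, but (14/21)/(28/28) = 0.667, a 33% fall.
- An unchanged daily user goes from 28 to 21 days, a 25% apparent drop, and is not a responder.
- Free-day rule, raw: (1.5F/21)/(F/28) = 2.0, so the rate of free days must double.

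The mismatch therefore loosens one rule and tightens the other.

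**Alternative reading.** If weeks 10–13 meant four calendar weeks (28 days), the window point would disappear. The free-day rule would then need 2 of 28 free days at F = 1 (1 − 26/27 = 3.7%) and 3 of 28 at F = 2 (1 − 25/26 = 3.8%), so the contradiction with Table 1 would remain.

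**The case against.** The strongest reply is that this is a drafting slip. The category labels say reduction, as Table 1 does, so the phrase about free days is probably the error and nobody intends to count unchanged daily users as responders. That may well be the intention. It does not settle the text, because the sentence that specifies the model names the other variable and the coding follows from that sentence.

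A second reply is that scaling of counts is a derivation detail which a condensed article leaves to the full protocol or analysis plan. This stands in part. Silence on scaling is not itself an error, so the window point holds only if raw counts are compared. The contradiction between the definitions does not depend on it.

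A third is that with zero free days a percentage increase is undefined, and the article does not say such participants would be responders. That is correct. It leaves the rule without an answer for daily users.

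Three stronger inferences are tempting and are not supported:
- **That the 21/28 mismatch lets unchanged users qualify.** It does not. The low bar comes from taking a percentage of a small or zero free-day count.
- **That the free-day rule never demands a 50% fall in use.** This is true on proportions, where the maximum is 41.7%. On raw counts a 51–75% fall is needed at 9 to 12 baseline free days.
- **That false responders would swamp the difference between arms.** This needs the baseline distribution of use and response rates by arm, and the article gives neither.

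**Conclusion.** The point holds. The response outcome has two incompatible definitions, and the analysis section also contradicts its own category labels. The free-day wording is undefined or trivially met at 0 baseline free days and needs only a 6–8% fall in use at 1 or 2. The use-day wording on proportions needs 50–56% at every eligible baseline. Putting both windows on one scale does not cure this; choosing one definition does.

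The window mismatch is a separate and conditional fault. On raw counts it lowers the use-day threshold from 50% to about 33–37% and doubles the free-day rate required.

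The conclusion assumes baseline free days of about 0 to 12. The window point further assumes that weeks 10–13 means 21 days and that raw counts are compared. How much the arm comparison would change depends on how many participants enter with few free days, which is not given. This is a secondary outcome; the primary endpoints and the sample size are unaffected. It should be corrected before database lock.

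**What to change.** Use one definition in Table 1 and in the analysis section, on the proportion of days used: a participant is a responder if (use days in the window / days in the window) ≤ 0.5 × (use days in the 28 days before baseline / 28).

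State the window. For the end-of-treatment analysis it is the 21 days before the week 13 interview. At the other visits listed in Table 1 it is each interview's own recall period, which is 21 days on treatment and 28 days at week 25. Delete the wording about an increase in cannabis-free days and keep the reduction labels.

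Baseline use is at least about 16 days for every eligible participant, so the denominator cannot be zero and no special rule for daily users is needed. The cost is a sentence or so in each place; no new data are required.

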	PCL-5 for Post Traumatic Stress Disorder (PTSD) [72]	20-item self-report measure of the 20 DSM-5 symptoms of PTSD. The four domains consist of: Re-experiencing, Avoidance, Negative alteration in cognition and mood and Hyper-arousal. Continuous (range 0–80)	Research Interview: Week 1 (baseline), 13 and 25
	Patient Reported Outcomes Measurement Information System (PROMIS-29) v2.1 [58]	29-item self-report measure assessing the past 7-days. The seven domains include: physical function, anxiety, depression, fatigue, sleep disturbance, ability to participate in social roles and activities, pain interference and intensity. A 5-point Likert scale (range 1–5) to measure symptom severity or frequency. Continuous (total and subscale scores converted to a z-scores)	Research Interview: Week 1 (baseline), 4, 7, 10, 13 and 25
**Social/ Other**	Treatment Satisfaction Questionnaire for Medication (TSQM) [73]	14-item questionnaire across four domains focusing on drug effectiveness, side effects, convenience and global satisfaction of the medication. Continuous (range 0–100)	Research Interview: Week 4, 7, 10, 13 and 25
	Drug Effects Questionnaire-5 (DEQ-5) [74]	5-item questionnaire assessing consumer ratings of drug effects. Continuous (range 0–7)	Research Interview: Week 4, 7, 10, 13 and 25
	Testing the Blind	2-questions exploring the participants’ subjective opinion of study drug allocation. Binary categorical (placebo vs CBD) and continuous (% confidence)	Research Interview: Week 1 (baseline), 4, 7, 10, 13 and 25
	Safety Adverse Events	Adverse events assessed with study clinician to assess for any side effects of study drug. Unbounded count	Research Interview: Week 1 (baseline), 4, 7, 10 and 13
	Treatment Retention	Calculated from treatment records and participant withdrawal/ completion form. Discrete numeric (week of dropout)	Clinical review: week 13
	Modified Everyday Discrimination Scale (m-EDS) [75]	10-item instruments based on the Discrimination/ Racism in Everyday Life and 6-item instrument based on Discrimination/ Racism in Healthcare adapted to a diverse Aboriginal and Torres Strait Islander context. Participants are asked to report the extent to which they experience discrimination in different settings, with the response options of ‘not at all’, ‘a little bit, ‘a fair bit’ and ‘a lot’. Continuous	Research Interview: Week 1 (baseline)

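### The single-count adverse-event model states no exposure term and calls its result a relative risk; if dropout differs by arm, the arm with more dropout looks modestly safer

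*Protocol article*

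**What the plan says.** All of this is in the protocol article.

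- **Single-count model.** Under Data analysis, Secondary outcomes, adverse events appear among the outcomes with one observation per person: "relative risk of adverse events during the trial period with negative binomial regression with log link function". The covariates for that group of outcomes are given as a list: "Group, number of counselling sessions attended, and whether or not NRT was taken will be the sole predictors in these models".
- **Repeated-measures model.** The same section also uses adverse-event count as its example of an unbounded count under the "random slopes mixed-effects models for repeated measures regressions with group, time, the group × time interaction, number of counselling sessions attended" and NRT. The article does not say which of the two models carries the safety comparison.
- **Form of the variable.** Table 1 has "Adverse events assessed with study clinician to assess for any side effects of study drug. Unbounded count", so a count and not a rate.
- **Who is analysed.** Under Participant numbers: "Participants who discontinue study procedures after commencing study interventions" after medication is dispensed on Day 1 "will not be replaced in the study but will be included in the modified intention-to-treat analyses".
- **Dropout is foreseen.** It is an outcome in its own right: "hazard of treatment dropout via discrete-time hazard model with complementary log–log link function". No expected rate is given.
- **Missing data.** The opening of Data analysis applies hierarchical multiple imputation to missing data in general. It does not say whether adverse events after dropout count as missing.
- **Observation window.** Table 2 schedules adverse-event assessment at weeks 4, 7, 10 and 13. Table 1 and the Clinical reviews section also list week 1.

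**The concern.** A total count grows with the time over which events can be recorded. A participant last assessed at week 4 has about 3 of 12 weeks observed, a quarter of the full period, but enters the single-count model on the same footing as a completer. If one arm loses more people, its mean count falls for a reason unrelated to how often events occur.

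Safety is the first secondary aim listed. If dropout were higher on CBD, the error would flatter CBD, which is the wrong direction for a safety statement.

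The label is a separate problem. Negative binomial regression with a log link on a total count yields a ratio of mean counts. It becomes a ratio of rates only when exposure is included, and it is never a ratio of proportions with an event. This holds whatever the dropout.

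**Working it through.** **1. The plan's own figure.** The only computed figure in the article is the sample size: d = 0.41, two-sided α = 0.05, 90% power, 125 per group. n = 2 × (1.960 + 1.282)² / 0.41² = 2 × 10.507 / 0.1681 = 125.0, which rounds up to 126 per arm (252 in all). Power at 125 per arm is 0.900. The figure reproduces and is not affected by this point. I use 125 per arm below.

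**2. What the single-count model estimates.** Suppose events occur at rate r per week while a person is observed for time e. The mean count is then r × E(e). With no exposure term and no stand-in for time, the fitted ratio is

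(true rate ratio) × E(e | CBD) / E(e | placebo).

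**3. Mean observed time.** Assume a constant dropout hazard that reaches proportion D by week 12. Then E(e) = −12·D / ln(1 − D).

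- D = 10%: 12 × 0.10 / 0.1054 = 11.39 weeks
- D = 20%: 12 × 0.20 / 0.2231 = 10.76 weeks
- D = 40%: 12 × 0.40 / 0.5108 = 9.40 weeks

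With equal true rates, the raw count ratio is 9.40 / 10.76 = 0.87 at 20% versus 40%, and 9.40 / 11.39 = 0.83 at 10% versus 40%.

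**4. The model with the plan's predictors.** Step 3 leaves out counselling sessions, which partly track time on study. A simulation adds them. Assumptions, none from the article: 2 events per 12 weeks, overdispersion 1, 85% attendance of sessions that fall while on study, 40% NRT, true ratio 1.00, nothing imputed. Session timing follows the Table 2 footnote (three in the first 6 weeks, one in weeks 7–13). There are 400 replicates. The early-clustering case puts 60% of expected events in the first 3 weeks. Entries are CBD-to-placebo ratios.

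| Dropout, placebo / CBD | Constant rate: plan's predictors | Constant rate: log-time offset, no counselling | Early clustering: plan's predictors | Early clustering: log-time offset, no counselling |
|---|---|---|---|---|
| 20% / 20% | 1.000 | 1.001 | 0.998 | 1.000 |
| 20% / 30% | 0.960 | 0.996 | 0.985 | 1.043 |
| 20% / 40% | 0.937 | 1.002 | 0.964 | 1.080 |
| 30% / 50% | 0.933 | 0.996 | 0.970 | 1.099 |
| 10% / 40% | 0.897 | 0.997 | 0.955 | 1.126 |

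The simulation error is small. With a mean count near 1.8, the standard error of one log ratio is about √(2 × (1/1.8 + 1)/125) = 0.158. Dividing by √400 gives about 0.008, so each entry is good to roughly ±0.02.

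**5. Further readings.**

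- *Direction.* With dropout reversed (40% placebo, 20% CBD, constant rate), the plan's predictors give 1.062. Again the arm with more dropout looks safer.
- *A real excess.* With a true ratio of 1.25 and 20% / 40% dropout, the plan's predictors give 1.158 and the offset model gives 1.247.
- *Counselling as a stand-in for time.* Without counselling or offset, the ratio at 20% / 40% is 0.878, a shortfall of 0.122. With counselling the shortfall is 1 − 0.937 = 0.063, so it removes (0.122 − 0.063)/0.122 = 48%. Over the constant-rate rows with unequal dropout the share is roughly 35–55%.
- *Interval counts.* A model of 3-weekly counts with time as a factor and log observed time in the interval as offset stays near 1.00 whether the rate is constant or events cluster early.

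**The case against.** The strongest reply is that the listed predictors do not rule out an offset. An offset has a fixed coefficient and is not a predictor. The same sentence also governs the discrete-time dropout model, which cannot be fitted sensibly without baseline time terms, and the list names none. The list may therefore cover substantive covariates only, with the rest left to the analysis plan. A reader might infer that the article forbids exposure adjustment, and the wording does not go that far. What remains is that the article gives the outcome form, family, link and covariates for this model, and followed as written it has no exposure term.

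Second, the article has another adverse-event analysis. Per-interval counts with a time factor largely deal with unequal follow-up, because a person who leaves contributes fewer intervals. This stands, and it defeats any reading that the trial's whole safety comparison ignores follow-up time. It also leaves two models with no stated order between them, and only the single-count one is tied to the reported ratio.

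Third, the general imputation rule could cover events after dropout and so reduce or remove the bias. That is possible. But a leaver's total is an observed, truncated number and not an obviously missing value, and the article does not say it would be imputed.

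Fourth, counselling attendance already absorbs part of the difference. It does, by about half at 20% versus 40%. But it is measured after randomisation, and three of its four sessions fall in the first 6 weeks, so it separates a week-7 leaver from a completer poorly.

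Fifth, a plain offset can do more harm than the omission when events cluster early: 1.08 to 1.13 against about 0.96 at 20% / 40% and 10% / 40% dropout. This stands and shapes the fix.

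**Conclusion.** The point holds as a conditional one. The single-count model as written has no exposure term, and its result is mislabelled as a relative risk. The bias needs two conditions: dropout that differs by arm, and later events that are neither collected nor imputed. The article does not settle either.

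Under the stated assumptions the size is modest. With the plan's own predictors, a constant event rate and no true difference, the ratio is about 0.93 to 0.94 at 20% versus 40% dropout and about 0.90 at 10% versus 40%. It is about 0.96 to 0.97 in those larger-gap scenarios if events cluster early, and 1.00 when dropout is equal.

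Two stronger readings are tempting and not supported. One takes the raw exposure ratio, 0.83 to 0.87, as the size of the bias; that leaves out the counselling covariate the plan includes. The other concludes that CBD will look safer than it is; nothing in the article indicates which arm will lose more participants, or that the arms will differ.

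This is a secondary analysis, and neither the primary endpoints nor the sample size is touched. The wording is still worth correcting, because the error is systematic, favours the arm with more dropout, and is easy to avoid.

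**What to change.** 1. Name the per-interval (3-weekly) negative binomial model as the adverse-event comparison, with time as a factor and log(observed time in the interval) as offset. Report an incidence rate ratio, and say how it is summarised over the intervals given the group-by-time term.
2. If a single-count model is kept, add log(time from first dispensing to last adverse-event assessment) as an offset. Note that this assumes a constant event rate and overcorrects, to about 1.08–1.13 in the two scenarios above, if events cluster early.
3. If a relative risk is wanted, report the proportion of participants with at least one event by arm.
4. State the adverse-event observation window, reconciling Tables 1 and 2 on week 1, and say whether events after dropout are collected, imputed or neither.

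The cost is a few sentences and a little extra analysis. Visit timing and week of dropout are already recorded. Week of dropout comes from treatment records, however, so the offset should be built from the adverse-event assessment dates, with dropout week as a check.
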